## Abstract

**Background:**

Seroma formation is a common complication after mastectomy and is associated with delayed wound healing, infection, skin flap necrosis, patient discomfort and repeated visits to the out patient clinic to deal with seroma and its sequelae. Closing the dead space after mastectomy seems to be key in reducing seroma and its complications. Various methods have been described to reduce the dead space after mastectomy: closed suction drainage, quilting of the skin flaps and application of adhesive tissue glues. The aim of this trial is to compare seroma formation and its sequelae in the various methods of flap fixation.

**Methods:**

This is a multicenter, double-blind, randomized controlled trial in female breast cancer patients undergoing mastectomy, with or without axillary clearance. Exclusion criteria consist of breast conserving therapy, direct breast reconstruction and incapacity to comprehend implications and extent of study and unable to sign for informed consent. A total of 336 patients will be randomized. Patients will be randomly allocated to one of three treatment arms consisting of flap fixation using ARTISS tissue glue with a low suction drain, flap fixation using sutures and a low suction drain or conventional wound closure (without flap fixation) and low suction drainage. Follow up will be conducted up to twelve months post surgery. The primary outcome is the number of seroma aspirations and secondary outcomes consist of number of out patient clinic visits, surgical skin infection rate, shoulder function, cosmesis, health-related quality of life and costs and cost-effectiveness (cost/QALY).

**Discussion:**

This is the first study of its kind to evaluate the effect of flap fixation and its sequelae (ie seroma aspirations, number of out patient clinic visits, infection, shoulder function, patient assessed cosmesis, quality of life and cost-effectiveness) in a double blind randomized controlled trial.

**Trial registration:**

This trial was approved by the hospitals’ joint medical ethical committee (**14-T-21,** 2 June 2014). The SAM Trial is registered in ClinicalTrials.gov since October 2017, Identifier: NCT03305757.

## Background

Seroma formation is a common side effect after surgery for breast cancer, with a highly variable cited incidence of 3% to more than 90% [1–3]. Seroma is a collection of serous fluid that contains blood plasma and/or lymph fluid. Seroma formation and its sequelae form the mainstay of complications in breast cancer surgery and some surgeons regard it as an unavoidable nuisance after breast cancer surgery. Complications vary from delayed wound healing, repeated seroma aspirations with the risk of infection, prolonged hospital stay, skin flap necrosis, patient discomfort, repeated visits to the out patient clinic, delay in commencing adjuvant therapies and higher surgical expenditures [2, 4, 5].

Many questions still remain with regard to the pathophysiology of seroma formation. Several factors have been held accountable for seroma formation, such as the use of electrocautery, extensive dissection in breast surgery and the extent of axillary lymph node involvement [6–9]. In the last decade, many publications have surfaced, focusing on the surgical prevention of seroma formation following mastectomy and/or axillary clearance. The success of all these interventions seems to have common ground: reduction of the dead space [10]. Closing the dead space after mastectomy can be achieved by closed suction drainage, quilting of the skin flaps or application of adhesive tissue glues to the skin flaps before wound closure [11–15]. There is however no consensus on which technique is most superior in reducing seroma formation and its sequelae [15]. In a randomized controlled trial published in 2010, the authors concluded that it was difficult to elucidate whether reducing the dead space or ligation of lymphatics or a combination of both were responsible for the reduction of seroma formation [16].

The electronic scalpel has been proven to enhance seroma formation after mastectomy [9]. No superior effect in seroma reduction has been seen in the use of other surgical devices (laser scalpel, argon diathermy and ultrasonic scalpel). Van Bemmel et al. concluded that seroma formation after axillary clearance cannot be avoided, but mechanical closure of the dead space leads to a significant reduction of seroma [10]. Several retrospective studies have shown that diminishing the dead space by means of flap anchoring can be very beneficial [17–20].

Until now one prospective randomized controlled trial has been published showing a significant reduction of seroma formation and seroma related complications after flap fixation using quilting sutures [21]. A review published by Van Bastelaar et al. concluded that mechanical flap fixation seems to reduce seroma formation and seroma aspiration after mastectomy with or without axillary clearance. Well executed randomized controlled trials are however needed to confirm these results [22]. The aim of the current randomized controlled trial (RCT) is to compare seroma formation and its sequelae in the various methods of flap fixation. The SPIRIT Statement guidelines were used for designing and describing this trial [23, 24].

## Study objectives

The primary objective of this RCT is to assess the effect of flap fixation using sutures or tissue glue on the number of seroma aspirations after mastectomy for breast cancer in the first year following surgery. Secondary objectives include assessment of the number of out patient clinic visits, infection rate, shoulder function, cosmesis, health-related quality of life, costs and cost-effectiveness.

## Methods

### Study design

The SAM (Seroma reduction After Mastectomy) Trial is a double blind randomized controlled trial. Patients will be allocated to one of three groups. The first group will undergo flap fixation using sutures and placement of low vacuum drainage, the second group will undergo flap fixation using ARTISS tissue glue and low vacuum drain placement and the third group will undergo conventional wound closure and low vacuum drainage.

### Setting

This multi center randomized controlled trial is ongoing at the time of publication and is being conducted at three different district hospitals (Zuyderland Medical Center Sittard, Albert Schweitzer Hospital Dordrecht and St Jansgasthuis Hospital, Weert), two of which are teaching hospitals (Zuyderland Medical Center Sittard and Albert Schweitzer Hospital Dordrecht). All hospitals are situated in the Netherlands.

## Participants

All patients will be recruited from the surgical breast cancer clinics after evaluation for invasive breast cancer or DCIS. Patients will be recruited in three breast cancer clinics, who together treat 1000 patients annually for breast cancer.

### Inclusion criteria

The inclusion criteria are as follows: (1) patients suffering from invasive breast cancer or DCIS with an indication for mastectomy with or without sentinel lymph node biopsy or modified radical mastectomy, (2) female sex, (3) older than 18 years of age.

### Exclusion criteria

The following exclusion criteria will be applied: (1) patients undergoing breast conserving therapy, (2) patients undergoing direct breast reconstruction, (3) patients unable to comprehend implications and extent of study and therefore unable to sign for informed consent.

### Recruitment

The study commenced in June 2014 and the first patient was enrolled on June 14th 2014. The study is still ongoing at the time of publication. Once patients have been screened with respect to the inclusion and exclusion criteria, they are informed about the trial by one of the breast surgeons. After informed consent has been obtained, baseline demographics are noted.

### Randomization

Randomisation is achieved using a web based randomization programme (ALEA, Software for Randomisation in Clinical Trials). Randomization will take place on the day of surgery, after the start of the operation and 30 min before wound closure. Blocked randomization will take place with randomly selected block sizes (6/9/12) with an allocation ratio of 1:1:1. Randomisation will be stratified per site. Both patients and surgeons will be blinded. Patients will be blinded throughout the trial and the surgeon performing the follow-up assessments is also blinded. To ensure blinding, patients will not be evaluated by their own surgeon during follow up. Patients will be allocated into one of three groups, (A) no flap fixation and placement of a low suction drain, (B) flap fixation using sutures and placement of a low suction drain, (C) flap fixation using tissue glue (ARTISS) and placement of a low suction drain.

### Study interventions

All procedures are performed by experienced breast surgeons. The nipple-areola complex is removed and dissection of the skin flaps is performed by using electrocautery. Removal of breast tissue from the pectoral muscle includes removal of the pre-pectoral fascia. All patients receive a low suction drain before closure of the skin. All procedures are performed as day cases unless comorbidities warrant hospital admission.

#### Conventional wound closure

After mastectomy and placement of a low suction drain, extent of the skin flaps will be measured and noted in the CRF. The skin edges will be sutured in one layer using absorbable monofilament sutures (Monocryl 3.0 or V-lok 30 cm), depending on the surgeon’s preference.

#### Flap fixation using sutures

After having performed the mastectomy, extent of the skin flaps is measured (in cm’s) from medial to lateral and from cranial to caudal. The skin flaps will be sutured on to the pectoral muscle using polyfilament absorbable sutures (Vicryl 3.0), placed at 4–5 cm intervals in two or three rows, depending on the extent of the skin flaps. The distance between all sutures is 4–5 cm. Care will be taken to prevent dimpling of the skin. The number of rows and total number of Vicryl sutures are noted in the CRF. The axillary area is not approximated using sutures. The skin edges will be sutured in one layer using absorbable monofilament sutures (Monocryl 3.0 or V-lok 30 cm), depending on the surgeon’s preference.

#### Flap fixation using ARTISS tissue glue

After having performed the mastectomy, extent of the skin flaps is measured (in cm’s) from medial to lateral and from cranial to caudal. ARTISS is applied as a 2 mL spray and used on both skin flaps. Care will be taken to make sure that the skin flap and pectoral muscle surfaces are dry before applying the glue. After the spray has been applied, compression on both skin flaps to the underlying muscle is applied for 3 min. The skin edges will be sutured in one layer using absorbable monofilament sutures (Monocryl 3.0 or V-lok 30 cm), depending on the surgeon’s preference.

All surgeons receive detailed live and video instructions on performing the various closure techniques to standardize closure techniques.

#### Drains

The drain is connected to a low suction drain bottle (Armstrongmedical) and drain output is noted daily. In patients undergoing mastectomy without axillary clearance, the drain is removed when drain output is less than 50 mL or after a maximum of 48 h, irrespective of drain output.. In patients undergoing modified radical mastectomy (including axillary clearance) the drain is removed if daily production is less than 50 mL or after a maximum of 5 days, irrespective of drain output. Patients never receive more than one drain.

##### Interleukin-6 and TNF-α sampling

Pro-inflammatory cytokines such as IL-6 and TNF- α are related to tissue damage. It is expected that patients with higher levels of the early systemic inflammatory response markers in seroma might suffer from increased seroma formation. The aim of this sampling was to assess if there was any association between IL-6 and TNF-α levels in seroma fluid measured on the first postoperative day and seroma and seroma related complications in patients undergoing mastectomy with or without flap fixation. Seroma samples will be collected on the first postoperative day for analysis of Interleukin-6 (IL-6) and Tumor Necrosis Factor (TNF-α). Drain fluid (10 ml) will be collected between 8 and 10 a.m. The samples are centrifuged at 1300 rpm for 10 min and stored at − 80 °C. Human Il-6 and TNF-α concentrations will be determined using in-house developed standard enzyme linked immunosorbent assays (ELISA). The sampling will be performed in one batch to ensure reliability of the sampling process.

##### Il-6 ELISA

96-well microplate (Greiner, 655,061) will be coated overnight at 4 °C with mouse anti- human IL6 (5E1). Hu IL6 (R&D Systems) will be used for standard titration curve. Standard and samples will be incubated for 2 h at room temperature (RT). Biotinylated polyclonal rabbit anti-human IL6 will be bound to captured human IL6. Streptavidin-peroxidase conjugate will be bound to the biotinylated antibody and reacted with the substrate, Tetramethylbenzidine (TMB). The enzyme reaction will be stopped by the addition of 1 M H_2_SO_4_. Spectrophotometry will be performed at 450 nm.

##### TNFα ELISA

96-well microplate (Greiner, 655,061) will be coated overnight at 4 °C with mouse anti- human TNFα (61E71; Celltech). rHu TNFα will be used for standard titration curve. Standard and samples will be incubated for 1 h at room temperature (RT). Polyclonal rabbit anti-human TNFα will be bound to captured human TNFα. Goat anti rabbit peroxidase (IgG HRP Jackson Immuno Research) will be bound to the secondary antibody and reacted with the substrate, Tetramethylbenzidine (TMB). The enzyme reaction will be stopped by the addition of 1 M H_2_SO_4_. Spectrophotometry will be performed at 450 nm.

### Study outcomes

#### Primary outcome

The primary outcome is the number of seroma aspirations, as measured by the number of needle aspirations performed during the first post-operative year. We decided on seroma aspiration as primary outcome, as this probably is the most objective assessment of clinically relevant seroma formation. There are strict criteria for seroma aspiration; the mere presence of seroma does not warrant aspiration. Seroma aspirations will be performed if 1) wound healing is at risk due to seroma (wound break down, seroma leakage, necrosis), 2) if there is discomfort or pain caused by large amounts of seroma, characterised by tenseness of the skin or 3) if there is contaminated/infected seroma and aspiration is necessary to treat infection. All patients that undergo seroma aspiration due to infection will also be treated with a 1 week course of Augmentin 625 mg 3 times daily. All surgeons and nurse practitioners participating in the study have received strict and clear instructions on when to perform seroma aspiration. Adherence to the aforementioned criteria is pivotal for assessing the primary study endpoint. As mentioned previously, all assessors have been blinded to the closure technique used.

#### Secondary outcomes

Secondary outcomes include:

1. The number of out patient clinic visits, measured during the first postoperative year. Patients with complications after mastectomy will have more frequent visits to the breast clinic.

2. Infection rate, as measured by 1) the need for antibiotics, 2) seroma aspiration due to infection or 3) surgical drainage during the first post-operative year.

3. Shoulder function, as measured using the DASH questionnaire (Disability of Arm, Shoulder and Hand, Dutch version). This will be assessed at baseline and at every postoperative visit to the outpatient clinic during one year after surgery. The DASH score has been proven to have a very good reliability and is able to differentiate between shoulder disability levels [6, 7].

4. Cosmesis, as measured using a scale questionnaire, assessed at every postoperative visit to the outpatient clinic during one year after surgery. Patients are questioned on the perceived aspect of their chest wall. Patients will be required to fill in a grading on a Likert scale, from 1 to 10.

5. Health related quality of life using the EQ-5D-5 L, societal costs and cost-effectiveness (cost per Quality Adjusted Life Year; QALY) with a time horizon of 12 months. The EQ-5D will be assessed at baseline, and at postoperative visits at 6 weeks, 3, 6 and 12 months. Costs will be measured with a retrospective cost questionnaire at baseline, and at postoperative visits at 3, 6 and 12 months.

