### Follow up

Follow up will be performed until one year after surgery. Patients will be evaluated in the out patient clinic 2 weeks, 6 weeks, 3 months, 6 months and 12 months postoperatively. A figure of the follow-up schedule is visible in Fig. 1. Subjects can leave the study at any time for any reason if they wish to do so without any consequences. The investigator can decide to withdraw a subject from the study for urgent medical reasons. Table 1 represents the time schedule of enrolment, interventions and assessments.

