**Fig. 1 Fig1:**
[figure not shown]
Follow-up schedule

**Table 1 Tab1:** Time schedule of enrolment, interventions and assessments

TIMEPOINT	Baseline	Day of surgery	Follow up					
	-t_1_	0	Day 1	2 wk	6 wk	3 m	6 m	12 months
ENROLMENT:								
Eligibility screen	X							
Informed consent	X							
*Demographics*	X							
Randomization		X						
INTERVENTIONS:								
Conventional wound closure		X						
Flap fixation using sutures		X						
Flap fixation using tissue glue		X						
ASSESSMENTS:								
Clinical assessment seroma and complications				X	X	X	X	X
Pain score				X	X	X	X	X
Patient reported cosmesis assessment				X	X	X	X	X
DASH	X			X	X	X	X	X
EQ-5D	X				X	X	X	X
Cost evaluation	X		X			X	X	X

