### Statistical analysis

Missing data will be imputed using stochastic regression imputation to prevent a loss of statistical precision and reduce the likelihood of biased estimates of treatment effect. Mean and standard deviation and absolute number and percentage will describe patient characteristics. Single and multiple ordinal regression analysis will be used to compute the difference in the number of seroma aspirations between the three groups. Secondary outcome parameters will be compared between groups using single and multiple ordinal regression that fits the distribution of that endpoint (e.g. continuous, binary, count). The primary analysis is an intention-to-treat analysis and therefore withdrawals and non-adherence will be analysed in the group to which they were randomized.

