### Cost effectiveness

For the economic evaluation, incremental cost-effectiveness ratios will be calculated based on the societal costs per QALY within 12 months. For calculation of the QALY, the EQ-5D-5 L will be assessed at baseline, and at postoperative visits at 6 weeks, 3, 6 and 12 months. Costs will be measured by a retrospective cost questionnaire at baseline, and at postoperative visits at 3, 6 and 12 months. Standard sensitivity analyses and non-parametric bootstrap analyses will be performed to address uncertainty about the cost-effectiveness ratio (s). Cost-effectiveness acceptability curves will be constructed to address the probability that either one of the techniques is cost-effective.

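### EQ-5D is not scheduled at the existing 2-week visit, so utility loss that resolves before 6 weeks gets no weight in the 12-month QALY

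*Protocol article*

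**What the plan says.** The protocol article gives the EQ-5D schedule in three places, and they agree.

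- Secondary outcomes, item 5: "The EQ-5D will be assessed at baseline, and at postoperative visits at 6 weeks, 3, 6 and 12 months".
- Cost effectiveness: "For calculation of the QALY, the EQ-5D-5 L will be assessed at baseline, and at postoperative visits at 6 weeks, 3, 6 and 12 months".
- Table 1: the EQ-5D row is marked at baseline, 6 weeks, 3, 6 and 12 months and is blank at 2 weeks.

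The 2-week visit itself is part of the plan. Under Follow up: "Patients will be evaluated in the out patient clinic 2 weeks, 6 weeks, 3 months, 6 months and 12 months postoperatively". Table 1 marks clinical seroma assessment, pain, cosmesis and DASH at that visit. For DASH, Secondary outcomes confirms it: "This will be assessed at baseline and at every postoperative visit to the outpatient clinic during one year after surgery".

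The utilities feed the economic evaluation, where "incremental cost-effectiveness ratios will be calculated based on the societal costs per QALY within 12 months". Costs come from a retrospective questionnaire at baseline, 3, 6 and 12 months; Table 1 also marks a cost evaluation on day 1.

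**The concern.** The baseline EQ-5D is taken before surgery and the next one comes 6 weeks after it. Any rule that joins the observed points draws a line across those 6 weeks and cannot see a fall and recovery between them.

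The trial has reason to care about this interval. Under Drains, the drain is removed within 48 hours, or within 5 days after axillary clearance, whatever the output, so fluid can collect in the weeks that follow. Under Primary outcome, the triggers for aspiration include discomfort, pain and threatened wound healing, which are states that a utility instrument is meant to value. Early discomfort from the fixation itself would be missed in the same way, so the gap need not favour any one arm.

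Costs and effects are also covered unequally. Resource use in the early weeks can enter the numerator of the cost-effectiveness ratio through the 3-month questionnaire, while a health loss confined to those weeks cannot enter the denominator. The Discussion presents cost-effectiveness as something not yet studied on this topic, so a complete QALY is worth having.

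**Working it through.** **The plan's own figure.** None is given. The article states no utility SD, no expected QALY difference and no rule for turning EQ-5D values into QALYs, so there is nothing to reproduce. The trapezoid (area-under-the-curve) rule and the sizes of the dips below are assumptions.

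**Inputs from the article.** EQ-5D times (Secondary outcomes, Cost effectiveness, Table 1); the 2-week visit (Follow up, Table 1); a 20-point absolute difference in the need for aspiration (Sample size).

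**Step 1: weights as planned.** With times in years at 0, 6/52, 0.25, 0.5 and 1, each value's weight is half the distance between its neighbours.

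| Time | Planned | With a 2-week point |
|---|---|---|
| Baseline | 0.058 | 0.019 |
| 2 weeks | none | 0.058 |
| 6 weeks | 0.125 | 0.106 |
| 3 months | 0.192 | 0.192 |
| 6 months | 0.375 | 0.375 |
| 12 months | 0.250 | 0.250 |

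The 2-week weight is (6/52 − 0)/2 = 0.0577. The weights from 3 months onward do not change.

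**Step 2: a dip seen only at 2 weeks.** Suppose utility is the same at baseline and 6 weeks and lower by d at 2 weeks. As planned, the QALY loss recorded is 0. With the extra point it is 0.0577 × d.

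| Assumed d | Per affected patient (0.0577 × d) | Between arms (× 0.20) |
|---|---|---|
| 0.05 | 0.0029 | 0.0006 |
| 0.10 | 0.0058 | 0.0012 |
| 0.20 | 0.0115 | 0.0023 |
| 0.30 | 0.0173 | 0.0035 |

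The last column takes the 20-point difference from Sample size and assumes that each patient who avoids aspiration also avoids one such dip.

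**Step 3: cross-check.** A loss of full depth lasting 3 weeks has area d × 3/52 = 0.0577 × d, the same as the triangle in Step 2. For d from 0.05 to 0.15 this gives 0.003 to 0.009 QALY per affected patient.

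**Step 4: what is not lost.** A loss of depth d still present at 6 weeks enters the planned QALY with weight 0.125, and later losses enter with the later weights. The gap concerns only what has resolved by 6 weeks.

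**The case against.** The case for leaving the schedule alone has weight. It is stated identically in three places, contains no contradiction, and gives four postoperative utilities in a year for one part of the last-listed secondary outcome. The article does not give the time course of seroma, so nothing in it shows that most of the burden resolves by 6 weeks; the primary outcome counts aspirations over the full year. Early burden is also recorded outside the QALY, through pain, DASH, cosmesis, seroma assessment, aspirations, visits and infection. The between-arm amount at issue is a few thousandths of a QALY at most, and nothing shows that it would change a cost-effectiveness conclusion. All of this stands, and it limits the point to a minor one. It does not remove the gap: none of those other measures enters the QALY.

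Timing is a further objection. The first patient was enrolled in June 2014 and inclusion was estimated at 40 months, which runs to about October 2017, the month of the cited registration. Many patients have probably passed the 2-week visit. That limits what the remedy can recover.

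A reader might go further and infer that QALYs will be left unadjusted for baseline utility, so that chance imbalance could swamp any real effect. The documents do not support this.

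- The article is silent on adjustment. Baseline EQ-5D and baseline costs are collected, and Statistical analysis foresees multiple regression without listing covariates: "Secondary outcome parameters will be compared between groups using single and multiple ordinal regression that fits the distribution of that endpoint". Such detail is commonly left to the full protocol or analysis plan.
- Under randomisation, chance imbalance is a matter of precision and not of systematic bias, and the planned bootstrap would carry that uncertainty into the results.
- The size depends wholly on assumptions. For a utility SD of 0.10 to 0.25 and 112 per arm, the standard error of the baseline difference is SD × √(2/112) = 0.013 to 0.033. Carried through the year with an assumed slope of 0.3 to 0.7, one standard error shifts an unadjusted QALY difference by 0.004 to 0.023. That exceeds the early effect in Step 2, but with no expected QALY difference stated, it cannot be said to exceed any real effect.

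**Conclusion.** The point holds in a limited form and is minor. As written, the plan gives no weight to utility loss that arises after surgery and resolves before 6 weeks, although a visit with other questionnaires already falls in that window. The amount missed is about 0.003 to 0.017 QALY per affected patient and about 0.0006 to 0.0035 QALY between arms. These figures rest on the trapezoid rule, dips of 0.05 to 0.30 centred on the 2-week visit, and a 20-point difference in patients affected.

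It would be too strong to say that seroma burden as a whole drops out of the QALY, or that the likeliest QALY difference lies in this window. The documents do not show where in the year the burden falls.

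**What to change.** 1. Mark EQ-5D at 2 weeks in Table 1, and add that time point in Secondary outcomes (item 5) and Cost effectiveness, for all patients still to reach the visit.
2. For patients already past it, run a sensitivity analysis that predicts 2-week utility from the 2-week DASH and pain scores, using the patients who have all three. If too few 2-week values are available to support that prediction, report the unmeasured interval as a limitation of the cost per QALY.
3. Optional, for precision only: estimate incremental QALYs with adjustment for the baseline EQ-5D already collected, repeated within each bootstrap sample.

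The cost is one short form at a visit where questionnaires are already completed, plus an amendment. The main drawback is partial availability: with recruitment well advanced, the 2-week values would come from later patients, and the prediction for the rest would depend on a model. Step 3 needs no new data.
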